## 4. STUDY POPULATION

### 4.1 Population

A total of 159 patients with early-stage oral cavity carcinoma (cT1-3, N0, M0); tumor location will be limited to the intraoral areas of mucosal lip, buccal mucosa, lower alveolar ridge, upper alveolar ridge, retromolar gingiva, retromolar trigone, floor-of-the-mouth, hard palate, or the mobile portion of the oral tongue.

### 4.2 Inclusion criteria

To be eligible to participate in this study, a subject must meet all of the following criteria:

- Newly diagnosed early-stage OSCC is defined as clinically T1-3, N0 (only when T3 is assessed based on tumor dimensions of  $>2$  cm and  $\leq 4$  cm with DOI  $>10$  mm) (see Appendix 2: Tumor Nodal Metastasis (TNM) Staging 8th Edition), without previous treatment of the neck.
- The patient is  $\geq 18$  years of age at the time of consent.
- The patient has no palpable lymph nodes in the neck.
- Clinical nodal staging (cN0) has been confirmed by ultrasound, CT, and/or MRI if performed (not mandatory).
- The patient is a candidate for transoral excision and SLNB.
- The patient has provided written informed consent authorization before participating in the study.

### 4.3 Exclusion criteria

A potential subject who meets any of the following criteria will be excluded from participation in this study:

- The patient has other pathologies than squamous cell carcinoma;
- The patient has recurrent primary OSCC;
- The patient has a history of treatment of the neck (neck dissection and/or radiotherapy);
- The patient has USgFNAC positive for lymph node metastasis;
- The patient has poorly controlled diabetes mellitus;
- The patient refused preoperative imaging workups.

A potential subject who meets the following criteria will be excluded for the contrast-enhanced CT of the head and neck only:

- The patient has had a previous allergic reaction after administration of contrast fluid.

#### 4.4 Sample size calculation

Since it is unlikely that FDG-PET/CT will detect micrometastases with a sensitivity high enough to refrain from (elective) neck dissection if FDG-PET/CT is negative, the focus of this study will be on a PPV high enough to avoid SLNB with second stage neck dissection if FDG-PET/CT is positive. The sample size calculation is made on the number of early-stage OSCC patients, who undergo FDG-PET/CT, needed to reduce reliably the number of (positive) SLNB procedures by 25%.

Unfortunately, no studies with histopathological examination of neck dissection specimens or SLNB and follow-up as reference standard are available which vary cut-off values of objective scoring parameters, e.g. SUVmax, to find a high PPV for the detection of occult lymph node metastases. All such studies focused on a high sensitivity or the combination of sensitivity and specificity, whereas for the present study particularly a high PPV is needed. The study of Peltenburg et al compared SUVmax and lymph node size with the outcome of USgFNAC (14). Although the sensitivity of USgFNAC is limited, its specificity is near 100%. In 52 patients with lymph nodes smaller than 10 mm (radiologically negative) SUVmax was >4.9 in 17 patients of whom 12 had USgFNAC positive lymph nodes. Thus, if patients with SUVmax >4.9 would undergo directly a neck dissection in at least 12 patients a SLNB (with neck dissection as a second stage operation if SLNB is positive) could correctly be avoided. Using this SUVmax cut-off value a reduction of SLNB of 32.7% can be obtained and only a few unnecessary neck dissections will be performed.

To show with an 80% power and a one-sided alpha of 0.05 that the reduction of SLNB of 0.327 is not inferior to 0.25, we need 143 patients. This sample size was calculated using the PASS power software, option: non-inferiority test for one proportion, exact test.

As explained before it is expected that 4.2% of patients have to be excluded because of positive USgFNAC after to FDG-PET/CT. Further drop-out rate for this study is expected to be 5%. After all, generally, patients want to have an extensive diagnostic work-up. FDG-PET/CT is a routine diagnostic examination with a limited burden on the patient. Therefore, a total drop-out rate of (not more than) 10% is expected. Accordingly, this study's population should consist of 159 patients to enable sufficient statistical power.

With the sample size of 143 patients, we expect 47 patients to have a positive FDG-PET/CT scan. Based on the study of Peltenburg et al, we anticipate 33 positive and 14 negative histopathological examination results (14). This results in a PPV of 0.70. Based on binomial exact calculation of the 95% confidence interval (CI), with 47 patients having a positive FDG-PET/CT and a PPV of 0.70, an associated 95% CI of 0.56-0.84 is

expected.

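### With the stated inputs, 143 patients give about 65% power for the primary comparison, not the stated 80%

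*Protocol*

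**What the plan says.** All the inputs are in Protocol section 4.4.

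- Planning proportion: 17 of 52 patients in a cited study, given in the text as "Using this SUVmax cut-off value a reduction of SLNB of 32.7% can be obtained".
- Bound to be excluded: 0.25, the targeted 25% reduction.
- Error rates and result: "80% power and a one-sided alpha of 0.05 that the reduction of SLNB of 0.327 is not inferior to 0.25, we need 143 patients".
- Method: "This sample size was calculated using the PASS power software, option: non-inferiority test for one proportion, exact test".
- Inflation: a total drop-out of at most 10% takes 143 to 159, and the section concludes that "this study's population should consist of 159 patients to enable sufficient statistical power".

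The same section then applies the planning proportion to the evaluable number: "With the sample size of 143 patients, we expect 47 patients to have a positive FDG-PET/CT scan". Since 0.327 × 143 = 46.8, the value 0.327 is in working use and is not a stray misprint.

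**The concern.** The expected count and the rejection threshold lie too close together for 80% power. About 47 positive scans are expected among 143, and the exact test needs 45. The standard deviation of the count is √(143 × 0.327 × 0.673) = 5.6, so the expected count is only about 0.3 standard deviations above the threshold ((46.8 − 45)/5.6). A test placed like that succeeds a little under two times in three.

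This is the only power statement in the Protocol, and the total of 159, repeated in the summary and in sections 3, 4.1 and 8.5, rests on it. An ethics committee, funder or later reader would take the risk of missing a true reduction of 32.7% to be 20%. A result that failed to exclude 25% would then be read as stronger evidence against FDG-PET/CT than it is.

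**Working it through.** **Inputs (all from section 4.4).** p0 = 0.25; p1 = 0.327 (17/52 = 0.3269); one-sided α = 0.05; target power 0.80; n = 143; one-sample exact binomial test.

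**Formulas.** The critical value r is the smallest integer with P(X ≥ r | n, p0) ≤ α. Power is P(X ≥ r | n, p1). X is binomial.

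**The stated size, n = 143.**

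- P(X ≥ 44 | 143, 0.25) = 0.0695, which is above 0.05.
- P(X ≥ 45 | 143, 0.25) = 0.0481, so r = 45.
- P(X ≥ 45 | 143, 0.327) = 0.653. With 17/52 unrounded it is also 0.653; with p1 rounded up to 0.33 it is 0.681.

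The stated 80% is not reproduced.

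**If nobody dropped out, n = 159.** r = 50, actual α = 0.0395, power = 0.660.

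**Size needed for 80% power at 0.327.** Exact power moves in a sawtooth as n grows, so two figures are needed.

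| n evaluable | r | actual α | power at 0.327 |
|---|---|---|---|
| 143 | 45 | 0.048 | 0.653 |
| 159 | 50 | 0.039 | 0.660 |
| 218 | 66 | 0.045 | 0.798 |
| 219 | 66 | 0.049 | 0.810 |
| 220 | 67 | 0.039 | 0.782 |
| 234 | 71 | 0.037 | 0.798 |
| 235 | 71 | 0.040 | 0.811 |

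The first n that reaches 80% is 219, and power stays at or above 80% from 235. Enrolment at 10% drop-out would be 219/0.9 = 243.3, so 244, or 235/0.9 = 261.1, so 262.

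**Could another method give 143 at one-sided 0.05?**

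- Normal approximation with null variance for α and alternative variance for power: n = [(1.645 × √(0.25 × 0.75) + 0.842 × √(0.327 × 0.673)) / 0.077]² ≈ 207.
- Null variance throughout: 196. Alternative variance throughout: 230.
- With continuity correction these three become 220, 209 and 243.
- Arcsine: 214.
- Exact test with the hypotheses reversed (null 0.327, true value 0.25): 220.

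None comes near 143. One-sided 0.025 moves further away: exact power at 143 is 0.514.

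**Two settings that do return 143.**

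- Exact test at one-sided 0.05 with p1 between 0.345 and 0.346. Here 143 is the smallest n with 80% power (power 0.802 at 0.345 and 0.810 at 18/52 = 0.346). This would fit 18 of 52 having been entered in place of 17 of 52.
- Normal approximation with null variance at one-sided 0.10: (1.282 + 0.842)² × 0.1875 / 0.077² = 142.6, rounded up to 143. This contradicts both the stated alpha and the stated exact test. The exact test at one-sided 0.10 has 77.5% power at 143.

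Each departs from something the section states, and the software output is not shown.

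**Drop-out step.** 143/0.9 = 158.9, so 159. This step is correct.

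**The case against.** The recomputed power is not in dispute. The fair objections concern what is built on it.

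- *The cause.* A miskeyed 18 of 52 is only a numerical match. The text uses 17 of 52, 0.327 and 47 of 143 consistently (18/52 would give 49.5), and a second route also returns 143. This stands: the cause is unproven. The error does not depend on it.
- *Restating the power at 0.345.* It is true that 143 patients give 80% power for a true proportion of 0.345 or more. But the Protocol offers no basis for 0.345, and such a value would be fitted backwards to the sample size. This stands as a reason to prefer restating the power at 0.327.
- *The threshold of 45.* It is the critical value of the stated test for exactly 143 evaluable patients and one scoring criterion fixed beforehand. Section 10.1 calculates the reduction per scoring criterion, and section 10.2 varies cut-offs within the study data. So 45 of 143 should not be presented as a complete success rule for the trial.
- *The consequence.* This is a single-arm diagnostic cohort in which scan results do not change surgical planning, and section 10.1 names no hypothesis test. The 35% risk therefore belongs to the test in section 4.4. That narrows the harm. But section 4.4 justifies the trial's size by that very test, so its power has to be right.

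**Conclusion.** The concern holds. From the Protocol's own inputs, 143 evaluable patients give 65.3% power, about 15 percentage points below the stated 80%, and the type II error is about 35% where 20% is implied. Reaching 80% would take at least 219 evaluable patients, 76 more than stated, and 235 to hold it at every larger size. The gap is far beyond rounding or differences between programs.

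The conclusion assumes an ordinary exact binomial test with exactly 143 evaluable patients, a true proportion of 0.327 and a scoring criterion fixed beforehand. It takes 17 of 52 as given and does not judge whether that is the right planning value for the endpoint. Because the wrong figure is the sole justification of the sample size, it must be corrected.

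**What to change.** Rerun the calculation from the stated inputs, keep the output on file, and correct section 4.4. The simplest correction keeps 143 evaluable and 159 enrolled and states that the exact test of 0.25 at one-sided 0.05 has about 65% power if the true proportion is 0.327. It may add, as information only, that 80% power applies to a true proportion of 0.345 or more. The sentence that 159 patients give sufficient power should be reworded to match.

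It also helps to state the critical value, at least 45 of 143, described as that of this test at exactly 143 evaluable patients and to be recalculated for the number actually analysed.

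The cost is protocol wording and a less favourable stated power. No extra patients are needed, and no procedure or clinical management changes. If the sponsor prefers to keep the 80% claim at 0.327, the price is 219 to 235 evaluable patients, or 244 to 262 enrolled at 10% drop-out.

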## **5. TREATMENT OF SUBJECTS**

### **5.1 Investigational product/treatment**

The diagnostic intervention of this study is one extra FDG-PET/CT before conventional treatment and questionnaires before treatment and after treatment (at 3, 6, 9, and 12 months).

### **5.2 Use of co-intervention (if applicable)**

After a fasting period of at least 6 hours, patients receive an intravenous injection of FDG. Approximately 60 min after the administration of the tracer a PET-low dose CT of the head and neck and chest abdomen (arms down) is acquired. After the PET-low dose CT a contrast-enhanced CT of the head and neck will be performed. To avoid false-positive results by cytological puncture, PET/CT has to be performed before USgFNAC. Patients with positive USgFNAC will be excluded for further analysis since the neck is not clinically negative.

### **5.3 Escape medication (if applicable)**

Not applicable.

**6. INVESTIGATIONAL PRODUCT**

Not applicable.

- 6.1 Name and description of investigational product(s)**
- 6.2 Summary of findings from non-clinical studies**
- 6.3 Summary of findings from clinical studies**
- 6.4 Summary of known and potential risks and benefits**
- 6.5 Description and justification of route of administration and dosage**
- 6.6 Dosages, dosage modifications and method of administration**
- 6.7 Preparation and labelling of Investigational Medicinal Product**
- 6.8 Drug accountability**

**7. NON-INVESTIGATIONAL PRODUCT**

Not applicable.

- 7.1 Name and description of non-investigational product(s)**
- 7.2 Summary of findings from non-clinical studies**
- 7.3 Summary of findings from clinical studies**
- 7.4 Summary of known and potential risks and benefits**
- 7.5 Description and justification of route of administration and dosage**
- 7.6 Dosages, dosage modifications and method of administration**
- 7.7 Preparation and labelling of Non Investigational Medicinal Product**
- 7.8 Drug accountability**

## 8. METHODS

### 8.1 Study parameters/endpoints

#### 8.1.1 Main study parameter/endpoint

The main study endpoint is the reduction of (positive) SLNB procedures for detection of (occult) cervical lymph node metastasis in cN0 OSCC patients by FDG-PET/CT.

#### 8.1.2 Secondary study parameters/endpoints (if applicable)

Secondary study endpoints are:

- Results of different scoring criteria, as interpreted by blinded review criteria for detection of occult lymph node metastases by FDG-PET/CT with a high PPV and accompanying sensitivity, specificity and negative predictive value using different FDG-PET/CT parameters and cut-off values:
  - Lymph nodes with FDG uptake exceeding normal physiological uptake will be considered positive / suspicious for lymph node metastases.
  - Visual scoring: A 5-point Likert scale will be used: 1, completely negative; 2, probably negative; 3, equivocal; 4, probably positive; 5, positive based on the local surrounding background.
  - Images will also be interpreted using the standardized Hopkins criteria. The Hopkins criteria use the internal jugular vein (IJV) and the liver as background blood pool reference (1 = uptake less than IJV, 2 = focal uptake greater than IJV but less than liver, 3 = diffuse uptake greater than IJV or liver, 4 = focal uptake greater than liver, 5 = intense uptake) (15).
  - Semi-quantitative scoring: All nodes with FDG-uptake and/or nodes of 3 mm or larger on PET/CT will be quantified by a manual volume of interest (VOI) drawing around these lymph nodes. SUV calculations are performed using the lean body mass corrected formula. As the maximum SUV value (SUVmax) is susceptible to artefacts such as noise and the SUVmean is observer-dependent, several other SUV metrics are explored, based on specified thresholds of the maximum uptake (SUV50, SUV70, SUV90). In total, 6 different standard uptake values (SUVmean, SUVmax, SUVpeak, SUV50, SUV70, SUV90) are calculated. Lesion-to-background ratios for 2 metrics (SUVmean and SUVmax) based on different background regions are calculated (liver and mediastinal blood pool

for whole body acquisitions and jugular vein, cerebellum, and muscle tissue for dedicated head and neck acquisition) which included ratios based on the liver, mediastinum, cerebellum, and several different muscle regions (16).

- Morphology: Of lymph nodes of 3 mm or larger the maximal axial diameter, minimal axial diameter, maximum longitudinal/short axis diameter ratio, non-fat low density, and shape (spheric or round) will be scored. These parameters may have additional value in combination with PET parameters.
- Inter-observer agreement between before and after scoring criteria are established;
- Quality of life will be explored with questionnaires. The following questionnaires will be used to measure the quality of life: EORTC QLQ-C30, EORTC-QLQ-H&N35, specific for head and neck cancer patients, EQ-5D-5L, and Shoulder Disability Questionnaire (SDQ) (17-19).
- Costs of different procedures will be collected for every patient arm from the electronic hospital records in every participating hospital and linked to Dutch unit costs. Both the Medical Consumption Questionnaire (MCQ) and the Productivity Cost Questionnaire (PCQ) will be sent to collect costs outside the hospital and productivity losses for each patient. The PCQ is a generic questionnaire designed to determine the costs of productivity losses. In addition, to gain detailed insight into the costs of surgery we aim to perform a microcosting study of SLNB and neck dissection using the Activity Based Costing Method.
- Patients' preferences and experience of the diagnostic procedures will be explored by qualitative research with semi-structured interviews based on an interview guide with a topic list with patients at the University Medical Center Utrecht and until data saturation has been reached.
- Additional (clinically relevant) findings of PET/CT, e.g. distant metastases and second primary tumors, will be scored and the effect on a treatment plan (change yes or no) and intent (curative or palliative) based on multidisciplinary team conference (MDTC) decisions will be analyzed.

### **8.1.3 Other study parameters (if applicable)**

Not applicable.

## **8.2 Randomisation, blinding and treatment allocation**

Not applicable.

## **8.3 Study procedures**

Patients diagnosed with cT1-3N0 OSCC scheduled for SLNB will be identified and screened for eligibility at the weekly multidisciplinary head and neck oncology meeting. If eligible, patients will be informed about this study. After the mandatory waiting period (three days, or more if applicable as long as needed), written informed consent will be obtained from patients and patients will be included.

Table 1. represents the process of participants during the study procedure.

## **8.4 Withdrawal of individual subjects**

Subjects can leave the study at any time for any reason if they wish to do so without any consequences. The investigator can decide to withdraw a subject from the study for urgent medical reasons.

### **8.4.1 Specific criteria for withdrawal (if applicable)**

Not applicable.

## **8.5 Replacement of individual subjects after withdrawal**

After the withdrawal of a subject before surgery, the subject will be replaced to obtain the intended 159 patients in the study group. If the subject withdraws after surgery, data of the subject till withdrawal will be used.

## **8.6 Follow-up of subjects withdrawn from treatment**

If the subject withdraws after surgery, data of the subject till withdrawal will be used.

## **8.7 Premature termination of the study**

In case the study is ended prematurely, the sponsor will notify the accredited METC within 15 days, including the reasons for the premature termination. Criteria for terminating the study prematurely are increased incidence of serious side effects in patients undergoing FDG-PET/CT.

## 9. SAFETY REPORTING

### 9.1 Temporary halt for reasons of subject safety

In accordance with section 10, subsection 4, of the WMO, the sponsor will suspend the study if there is sufficient ground that continuation of the study will jeopardize the subject health or safety. The sponsor will notify the accredited METC without undue delay of a temporary halt including the reason for such an action. The study will be suspended pending a further positive decision by the accredited METC. The investigator will take care that all subjects are kept informed.

### 9.2 AEs, SAEs, and SUSARs

#### 9.2.1 Adverse events (AEs)

Adverse events are defined as any undesirable experience occurring to a subject during the study, whether or not considered related to diagnostic intervention an extra FDG-PET/CT. Adverse events classified according to the CTCAE v.5.0 criteria grade 3 or higher, reported spontaneously by the subject or observed by the investigator or his staff will be recorded. This accounts for all adverse events that occur within the period from FDG intravenous injection until 2 hours after injection. It is not expected that any later occurring events can be attributed to the injection of FDG.

#### 9.2.2 Serious adverse events (SAEs)

A serious adverse event is any untoward medical occurrence or effect that

- results in death;
- is life-threatening (at the time of the event);
- requires hospitalisation or prolongation of existing inpatients' hospitalization;
- results in persistent or significant disability or incapacity;
- is a congenital anomaly or birth defect; or
- any other important medical event that did not result in any of the outcomes listed above due to medical or surgical intervention but could have been based upon appropriate judgment by the investigator.
- an elective hospital admission will not be considered a serious adverse event.

The investigator will report all SAEs to the sponsor without undue delay after obtaining knowledge of the events.

This study is expected to pose a negligible risk for patients; any serious adverse events occurring during 2 hours after injection are expected to be related to the standard treatment and not to the study intervention. Because of this, SAEs that results in death or are life

threatening will not be reported expedited through the web portal *ToetsingOnline* to the accredited METC that approved the protocol. The SAEs will be documented by the investigator and will be reported once a year.

#### **9.2.3 Suspected unexpected serious adverse reactions (SUSARs)**

Not applicable.

#### **9.3 Annual safety report**

Not applicable.

#### **9.4 Follow-up of adverse events**

All AEs will be followed until they have abated, or until a stable situation has been reached. Depending on the event, follow-up may require additional tests or medical procedures as indicated, and/or referral to the general physician or a medical specialist. SAEs need to be reported till end of study within the Netherlands, as defined in the protocol.

#### **9.5 Data Safety Monitoring Board (DSMB) / Safety Committee**

Not applicable.

## 10. STATISTICAL ANALYSIS

All data is analyzed with professional statistics software (IBM SPSS Statistics Version 26.0). Data are expressed as mean, standard deviations (for parametric continuous variables), and as median and quartiles (for nonparametric continuous variables). The number of cases and percentages are presented as categorical variables. Normal distribution will be verified by using the Shapiro-Wilk test. A p-value of  $< 0.05$  was regarded as statistically significant.

### Handling missing Data

Missing data will be handled using multiple imputation strategies. Results across multiple imputation data sets will be combined using the Rubin rules. LASSO-based logistic regression analysis will be used to identify the optimal panel for distinguishing patients with metastases from those without. This method is suitable for regression with a large number of variables and a relatively limited number of events and protects against overfitting. To estimate discriminative value we will compute the area under the curve (AUC) of the Receiving Operator Characteristic Curve (ROC).

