The number of SLNB procedures and second stage CND can be reduced by performing direct neck dissection without SLNB procedures in patients in whom occult LNM can be predicted with very high PPV by FDG-PET/CT. By varying cut-off levels scoring criteria can be developed and optimized to predict the presence of lymph node metastases with high PPV instead of high sensitivity, which is usually done. When focused on high PPV the sensitivity will probably be lower, but missed LNM will then be detected by SLNB when performed after negative FDG-PET/CT.

This proposed prospective multicenter study aims to develop FDG-PET/CT scoring criteria through which occult LNM in patients with early-stage OSCC are detected with high PPV,

reducing the number of SLNB needed. SLNB has a high sensitivity and negative predictive value to detect occult LNM but is invasive. When positive it warrants a second stage neck dissection with a higher risk of complications than when performed at the same stage as resection of the primary tumor. This affects the quality of life. Moreover, it is possible that FDG-PET/CT also finds occult LNM otherwise undetected by SLNB, improving survival.

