### Secondary Objective(s)

The secondary objectives of this study are:

- To optimize scoring criteria for the detection of (occult) lymph node metastases by FDG-PET/CT with a high positive predictive value.
- To assess the sensitivity, specificity, PPV, negative predictive value and accuracy for the different scoring criteria.
- To investigate inter-observer agreement before and after scoring criteria are established.
- To compare the quality of life and costs in three different diagnostic scenarios 1) PET/CT, 2) SLNB, and 3) PET/CT and, only if negative, SLNB.
- To obtain insight into patients' preferences and experience of the diagnostic procedures.

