#### 10.1 Primary study parameter(s)

Per (newly developed) scoring criteria the reduction of (positive) SNLB procedures will be calculated as well as the number of unnecessary neck dissections (accompanying false positives).

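### The blanket multiple-imputation rule does not exempt PET/CT results, so, read as written, a patient whose criterion cannot be scored is partly counted as an SLNB avoided

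*Protocol*

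**What the plan says.** Section 10, under the missing-data heading, gives one general rule: "Missing data will be handled using multiple imputation strategies". It continues "Results across multiple imputation data sets will be combined using the Rubin rules". No variable is named or exempted. The same paragraph then describes LASSO selection of the panel that separates patients with and without metastases.

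Section 10.1 defines the primary calculation: "Per (newly developed) scoring criteria the reduction of (positive) SNLB procedures will be calculated". It has no rule for a patient in whom a criterion cannot be scored.

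The introduction says which patients would skip SLNB. The saving comes from "performing direct neck dissection without SLNB procedures in patients in whom occult LNM can be predicted with very high PPV by FDG-PET/CT". The third diagnostic scenario in the secondary objectives is "PET/CT and, only if negative, SLNB".

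Section 4.3 keeps patients with a previous contrast allergy in the study; they "will be excluded for the contrast-enhanced CT of the head and neck only". Section 8.1.2 nevertheless lists morphology items, among them non-fat low density, and criteria that use the liver or other reference regions.

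**The concern.** The primary parameter counts what a strategy would do. For a patient with no usable result on a criterion, the strategy as described offers no route to skipping SLNB, so the contribution to the reduction is zero. Multiple imputation replaces that zero with the proportion of imputed data sets in which the patient comes out positive, and pooling carries the fraction into the estimate. This does not need a poor imputation model. Even a well-specified one answers what the reduction would be if every scan could be scored, which differs from the reduction that the strategy delivers.

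Two things are at stake. The reduction is set against a 25% benchmark in the sample-size section, and the planned 0.327 is not far above it. Criteria are also to be compared with one another, and imputation removes the penalty that a frequently unscorable criterion should carry.

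**Working it through.** **Inputs.** From section 4.4: assumed reduction 0.327, benchmark 0.25, 143 evaluable patients, one-sided alpha 0.05, "non-inferiority test for one proportion, exact test". The unscorable share m is not in the protocol; I assume 3, 7 or 14 of 143 patients (2.1%, 4.9%, 9.8%).

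**The plan's own figures.** 17/52 = 0.327. 143 × 0.327 = 46.8, the 47 expected positives. 143/0.90 = 158.9, hence 159. For 143 patients the exact test of 0.25 passes at 45 or more positives (actual alpha 0.048). Its power at 0.327 is 0.65, not the stated 80%. That is a separate matter, and nothing below depends on it.

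**Formula.** Let p be the positive rate among scored patients and q the mean imputed probability of a positive result among the unscorable.
- Reported after imputation: p(1 - m) + qm
- Delivered by the strategy: p(1 - m)
- Overstatement: qm, which is never negative

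If values are missing at random and no auxiliary variable is informative, q = p. The reported figure is then p, and it exceeds the strategy's figure by the factor 1/(1 - m).

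**Numbers at p = 0.327, n = 143.**

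| Unscorable | Strategy reduction | Reported | SLNBs credited | Factor |
|---|---|---|---|---|
| 3 (2.1%) | 140 × 0.327/143 = 0.320 | 0.327 | 3 × 0.327 = 1.0 | 143/140 = 1.02 |
| 7 (4.9%) | 136 × 0.327/143 = 0.311 | 0.327 | 7 × 0.327 = 2.3 | 143/136 = 1.05 |
| 14 (9.8%) | 129 × 0.327/143 = 0.295 | 0.327 | 14 × 0.327 = 4.6 | 143/129 = 1.11 |

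The strategy's reduction would fall to the benchmark at m = 1 - 0.25/0.327 = 23.5%.

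**Effect on a test against 0.25 (approximation).** Suppose the strategy's true reduction is exactly 0.25. The positive rate among scored patients is then 0.25 × 143/136 = 0.263 with 7 unscorable, or 0.25 × 143/129 = 0.277 with 14. A complete-case exact test, standing in for imputation without informative auxiliaries, passes at 43 of 136 or 41 of 129. The chance of passing is 0.096 or 0.175. With unscorable patients counted as SLNB not avoided and the cut kept at 45 of 143, it is 0.047 or 0.045.

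**The case against.** A reader might infer that the protocol orders imputation of PET/CT results and bases the primary count on imputed data. It says neither. The rule stands beside the LASSO text and could be meant for model building only, and an analysis plan not shown here could narrow it. That stands as a limit on certainty. It does not remove the point, because the protocol states a general rule without exception, in the paragraph on building the PET/CT panel, and nothing in section 10.1 overrides it.

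A reader might also infer that a large share of patients is affected. The documents do not support that. The one clearly documented gap is the missing contrast CT, and section 3 accepts the low-dose PET/CT as sufficient for participation. Visual and SUV scores do not need contrast, and node diameters and shape may still be measurable, so mainly one morphology item is touched. On the liver, section 3 limits the scan to head, neck and chest while section 5.2 adds the abdomen. If the liver really were outside the range, liver-based scores would be missing for nearly everyone, which is a scan-range inconsistency to reconcile rather than a 5 to 10% imputation problem.

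The error rates of 0.096 and 0.175 should not be read as properties of the planned primary analysis. They are complete-case approximations at assumed shares, and the test against 0.25 appears only in the sample-size section. Other measurements from the same scan could make imputed values more accurate; that would change q but would not make the overstatement negative.

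Finally, in a development study, performance when a criterion can be scored is a legitimate target. It is a different quantity from procedures saved, and it can be reported alongside.

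**Conclusion.** The point holds as a conditional one. Applied as written, the imputation rule would overstate the primary parameter, because patients without a scorable result would contribute fractional avoided SLNBs that the strategy does not deliver. The overstatement is about 2% of the true value with 3 of 143 unscorable, 5% with 7 and 11% with 14. In absolute terms that is 0.327 reported against 0.320, 0.311 and 0.295.

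This rests on three assumptions: that the rule reaches index-test values and the primary count, that imputed positives occur at the observed rate, and that the unscorable share lies in the range shown. At 2% the effect is small. It falls mainly on contrast-dependent morphology and reference-region criteria, so the distortion is as much in comparing criteria as in the headline figure.

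**What to change.** Add to sections 10 and 10.1, in words such as: *For the SLNB-reduction endpoint and the strategy scenarios, a patient in whom a criterion cannot be scored (scan unreadable, contrast CT required by the criterion not done, reference region not imaged) is counted as SLNB not avoided. The number unscorable is reported for each criterion. A patient with no FDG-avid or measurable node has a negative result and is not unscorable.*

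Keep multiple imputation for covariates in model building and for questionnaires. When a fitted model is then applied to count SLNBs saved, a patient lacking an item that it requires falls under the rule above.

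This is a counting rule for the analysis; it needs no extra data or patients and changes nobody's care. Its cost is a slightly less favourable reported reduction, and a lower chance of reaching 45 of 143 if the scored positive rate is 0.327: 0.65 with none unscorable, 0.59, 0.49 and 0.33 with 3, 7 and 14.
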